**Sample size**

Based on data from the Australian Bureau of Statistics, we anticipate approximately 89 Aboriginal youth turning 15 years old each month in Perth over the study period.
^
32
^ Using the primary outcome definition, monthly numbers of young people before their 15
^th^ birthday fully vaccinated against HPV, will be the unit of aggregation in the regression models. A total of 72 monthly data points (2020-2025) will provide 85% power to detect a one-standard-deviation shift in the average proportions post-intervention, at an α = 0.05 and a first-order autoregressive model with autocorrelation of 0.3.
^
38
^ Empirical research has shown autocorrelations of the order of 0.3 (median 0.33; IQR 0.03, 0.58; 36 ITS studies in public health).
^
39
^

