## Introduction

Human papillomavirus (HPV) is a common sexually transmitted infection that can lead to HPV-related cancers such as cervical cancer and other cancers such as anal, vaginal, and penile cancer.
^
1,
2
^ HPV rarely produces symptoms and cannot be cured or treated; therefore, vaccination is essential to protect against HPV and HPV-related diseases.

In 2007, Australia initiated the HPV vaccine through the National Immunisation Program (NIP) to girls aged 12 to 13 years in 2007 and to boys in 2013; catch up programs were implemented for older age groups. Up until 2023, the HPV vaccine provided as a free two-dose program for both males and females aged 12-13 years, with doses given between 5-6 months apart through school-based programs.
^
3
^ Responding to the global decline in HPV vaccination, lack of access to the vaccine and cost and burden required for two doses, WHO released updated recommendations in 2022 that a single dose was effective in reducing HPV.
^
4
^ As of 2023, Australia has transitioned to the single dose for 12-13 year olds through the NIP delivered at school with young people up to 26 years old also eligible for the free HPV vaccine. If a vaccine dose is missed at school, depending on their place of residence, a young person may receive a free catch-up dose at their school, their local Aboriginal or government health centre, or private general practitioner.

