### Immunisation program impacts

In Australia, the prevalence of the HPV types in women aged 18 to 24 years old which were targeted by the vaccine declined significantly from 28.7% in the pre-vaccination era (2005-2007), to 2.3% in vaccinated women after vaccine introduction (2010-2012).
^
5
^ The rate of high-grade cervical disease has also declined dramatically, by 2014 it dropped to less than half the 2007 rate in women under 20 years of age.
^
5
^ The introduction of the Gardasil 9 vaccine is expected to prevent up to 90% of cervical cancers. Some research suggests that increased HPV vaccination, together with greater participation in screening, has the potential to eliminate cervical cancer in Australia and elsewhere within a few decades.
^
5,
6
^

In Australia, young Aboriginal and Torres Strait Islander (hereafter, respectfully, Aboriginal) people do not receive their HPV vaccine dose, resulting in missed opportunities to be protected from HPV-related cancers.
^
4
^ This is particularly important as rates of cervical cancer in Aboriginal women are twice those of non-Indigenous women, mortality rates more than three times higher, and screening participation rates lower.
^
6–
9
^ The recent change to one HPV dose will have substantive impact on meeting the recommended dose proposed by WHO.
^
4
^ In 2022, the Australian national rate of having at least one dose of HPV vaccination for young people turning 15 years old was 83.0% for Aboriginal females and 78.1% for Aboriginal males.
^
10
^ In Western Australia (WA), the completion rates were 81.4% of Aboriginal females and 78.6% of Aboriginal males. Despite these overall rates being reasonable, there are pockets of concern within Western Australian, including the capital of the State, Perth. In 2022, 51% of Aboriginal young people in Perth received one dose of HPV vaccine during Year 7 and this did not improve in 2023 (unpublished data).
^
11
^ Substantive resources are needed to improve these rates both in school catch-up programs and within the community. To eliminate cervical cancer, improving HPV vaccine rates amongst young Aboriginal people is necessary.

Despite the decline in HPV, there are a number of reported barriers associated with HPV vaccine uptake including adolescents’ lack of awareness and knowledge, not feeling informed, and parental concerns around sexual activity and vaccine safety.
^
12

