**Data analysis**

*Interrupted time series*

A linear, segmented interrupted time series analysis will be used to evaluate the impact of the social media programme on HPV vaccination.

For the primary outcome, we will count the number of youths aged between 12 and before their 15
^th^ birthday who have received the HPV vaccination per month. Similarly, for the secondary outcome, we will count the number of young people aged up to 25 (inclusive) who have received the HVP vaccination per month. Our analysis models will include two segments: a pre-interruption period of 49 months, beginning on Jan 2020-Dec 2023, and a post-interruption period of 24 months, beginning on Jan 2024-Dec 2025, which encompasses both the intervention and post-intervention periods.

For each outcome, we will fit the following statistical model (Model 1), separately for the intervention and control series:

$$\text{Model}\;1:\log Y_{t}=\beta_{0}+\beta_{1}t+\beta_{2}I+\beta_{3}\left(t-T_{I}\right)I+\text{seasonal}+\text{offset}+\epsilon_{t}$$
where

$Y_{t}$
 is the outcome value at time t, and

$T_{I}$
 is the time of the interruption. The variable

I
 indicates the post-interruption segment, which is equal to 1 post the interruption and 0 before. Parameter

$\beta_{0}$
 is the intercept at the beginning of the series,

$\beta_{1}$
 is the slope in the first segment,

$\beta_{2}$
 is the level change between the expected value (based on the pre-interruption data) and the observed data, and

$\beta_{3}$
 is the difference in slope compared to

$\beta_{1}$
. The error term,

$\varepsilon_{t}$
 represents deviations from the fitted model, and we will assume these to have lag-1 autocorrelation. Seasonality will be accounted for by including two pairs of sine and cosine harmonics with periods of 12 and 6 months.
^
40,
41
^ Due to the changing of the vaccine schedule in the year following the interruption, the seasonal components will be phase shifted by six months for that year. The log of the relevant population (i.e. all Aboriginal youth aged between 12 and before their 15
^th^ birthday per month) will be included as an exposure offset to adjust for any changes to the population over time. We will assume a negative binomial distribution with a log link function. We will fit these models using the glarma package in R.
^
42
^

The effect measures of interest will be:

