## Discussion

This project aims to improve HPV vaccination rates amongst young Aboriginal people. Nationally, 75% of Aboriginal females and 68% of Aboriginal males receive their full course of the HPV vaccine at 15 years of age, however, there is substantial variation between states and territories. Given that the vaccine reduces the risk of cervical cancer, which has a high mortality rate in Aboriginal women, improving HPV vaccine rates is essential. Our project will combine health messages co-created by young people and implemented by micro-Influencers to improve HPV vaccination. Our vision is to develop campaign that can be implemented by other Aboriginal communities, settings and populations across Australia to improve HPV vaccination.

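### The number of doses that counts as the primary outcome before 2023 is not fixed, so the single pre-campaign trend may contain a definitional step at the two-dose to one-dose change

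*Protocol article*

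**What the plan says.** The Introduction describes the schedule change. "Up until 2023, the HPV vaccine provided as a free two-dose program for both males and females aged 12-13 years"; then "As of 2023, Australia has transitioned to the single dose for 12-13 year olds through the NIP".

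The primary outcome is worded in three ways:

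- **Outcomes:** being a recipient of the vaccination before the 15th birthday, with no number of doses.
- **Sample size:** presented as applying the primary outcome definition, the monthly number of young people before their 15th "birthday fully vaccinated against HPV, will be the unit of aggregation in the regression models".
- **Data analysis:** the number of youths aged 12 to before their 15th "birthday who have received the HPV vaccination per month", again with no number of doses.

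The Data analysis section sets "a pre-interruption period of 49 months, beginning on Jan 2020-Dec 2023" and gives that whole period one trend: β1 "is the slope in the first segment". Neither Model 1 nor Model 2 has a level or slope term at 2023. The only allowance for a schedule change is a six-month phase shift of the seasonal terms, placed in the year after the interruption.

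**The concern.** In an interrupted time series, the pre-interruption line is the counterfactual. About 36 of its months fall under a two-dose schedule and the last 12 under a one-dose schedule. 'Fully vaccinated' naturally means completing the schedule in force: two doses to the end of 2022, one dose from 2023. Young people who would have stopped after one dose are then non-events before 2023 and events afterwards, so the series steps up with no change in behaviour.

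A straight line fitted through such a step is too steep. Extrapolated past the interruption it overshoots, and the shortfall appears as a negative change in slope. Change in slope is one of only two effect measures named for the campaign, and the bias would work against finding a benefit.

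Model 1 is fitted to each series alone, and the sex and location subgroups use Model 1 on the intervention series only, so these fits have no protection. Model 2 removes only the part of the step shared with the control series.

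**Working it through.** **The plan's own figure.** The article gives no figure for this effect. Its neighbouring power figure reproduces as a simple mean shift of 1 SD: 48 + 24 months, AR(1) 0.3 and two-sided 5% give a standard error of 0.332 SD, so power = Φ(1/0.332 − 1.96) = 85.4%, against 85% stated. The effect sized for is therefore a 1-SD shift in the post-period average.

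**Inputs for the step.**

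- At least one dose by 15, national, 2022 (Immunisation program impacts): "was 83.0% for Aboriginal females and 78.1% for Aboriginal males".
- Full course, national, year not stated (Discussion): "75% of Aboriginal females and 68% of Aboriginal males receive their full course of the HPV vaccine at 15 years of age".
- Gap: 83.0 − 75 = 8.0 points in females; 78.1 − 68 = 10.1 points in males.
- Ratio and log step: 83.0/75 = 1.107, log 0.1014; 78.1/68 = 1.149, log 0.1385.

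**Assumptions.** The step is immediate at the start of 2023, its ratio carries over to the monthly rate, and there is no campaign effect.

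**Hand calculation.** Take a unit step at January 2023, months numbered 0 to 71, interruption at month 48, no harmonics, independent errors. Model 1 is then two separate straight lines.

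- False pre-slope: Σ(t − 23.5) over the last 12 months = 12 × (41.5 − 23.5) = 216; Σ(t − 23.5)² over 48 months = 48 × (48² − 1)/12 = 9212; β1 = 216/9212 = 0.02345.
- Counterfactual at month 48: 0.25 + 0.02345 × 24.5 = 0.8245. The true level is 1, so β2 = +0.1755.
- The true post-slope is zero, so β3 = −0.02345.
- At three months: 0.1755 − 3 × 0.02345 = +0.105.
- At December 2025 (month 71): 0.1755 − 23 × 0.02345 = −0.364.

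Multiplying by the log step and exponentiating:

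| | Females | Males |
|---|---|---|
| Slope change per year | exp(−12 × 0.02345 × 0.1014) = 0.972 | exp(−12 × 0.02345 × 0.1385) = 0.962 |
| Level change at three months | exp(0.105 × 0.1014) = 1.011 | exp(0.105 × 0.1385) = 1.015 |
| Observed against counterfactual, December 2025 | exp(−0.364 × 0.1014) = 0.964 | exp(−0.364 × 0.1385) = 0.951 |

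**Range over specifications.** I varied the step month (January or February 2023), the interruption month (48 or 49, because January 2020 to December 2023 is 48 calendar months but is stated as 49), the harmonics (none, or 12 and 6 months, not phase-shifted) and the AR(1) coefficient (0 or 0.3). The ranges on the log scale are:

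- Slope change: −2.2% to −2.9% per year in females, −3.1% to −3.9% in males.
- Three-month level change: 0.01 to 0.16 of the step, a rate ratio of about 1.00 to 1.02.
- December 2025 gap: 0.27 to 0.39 of the step, so 2.7% to 3.9% below in females and 3.7% to 5.2% below in males.
- Average post-period shift: −0.02 to −0.15 of the step, at most 0.152 × 10.1 = 1.5 points.

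A log-link count fit with offset gives nearly the same: slope −2.5% to −4.0% per year, and 3.1% to 5.8% below at the end.

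**After the fix.** One dose counted in every year makes the definitional step zero, and all these terms vanish. With 'fully vaccinated' kept and a January 2023 level term added, the bias in β1, β2 and β3 is also zero.

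**The case against.** **The break is conditional.** This stands. The Outcomes and Data analysis wording does not say 'fully vaccinated', and one dose throughout gives no definitional step. The Outcomes section also ties the definition to international and national reporting standards, which may settle the dose count but are not reproduced. Even so, the Sample size section presents its wording as the primary outcome definition, so it cannot be dismissed as a stray phrase.

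**The step is poorly known.** This also stands. An undated national figure is set against a 2022 one. Western Australian completion rates of 81.4% and 78.6% are quoted too. Read literally as full course, they differ from the national one-dose figures by only 83.0 − 81.4 = 1.6 and 78.1 − 78.6 = −0.5 points, and the artefact would be close to nil. Because the single dose applied to 12-13 year-olds, a measure at age 15 might also ramp rather than jump.

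**The control series helps.** Partly. The change was national, so Model 2 removes what both groups share. A difference between the groups in the one-dose to full-course gap would remain, and the article gives no control figures to size it.

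**Stronger readings.** A reader might infer that the artefact exceeds the effect the study is sized for, because 8 to 10 points is about two binomial SDs (√(0.8 × 0.2/89) = 4.24 points, assuming n = 89 and p = 0.8). But the raw step is not the bias: the average post-period shift is at most 1.5 points, under 0.4 of that SD. A reader might also multiply the false slope by 23 months and get about half the step; that leaves out the opposite-signed level change. Lastly, a reader might infer a large false rise from counting both doses. Even a full halving of the count in 2023 would give only 21% to 31% above the counterfactual by December 2025. It would need every youth to have had two doses and each to be counted twice, whereas the Data analysis section counts youths, not doses.

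**Conclusion.** The point holds in conditional form. The article words its primary outcome inconsistently and leaves the pre-2023 dose count open, while one pre-interruption slope spans the schedule change with no term for it. If 'fully vaccinated' is applied by the schedule in force, the harm falls on the change in slope and runs against the campaign; the three-month level change is little affected. The estimated size of 2.2% to 3.9% per year rests on the national figures being comparable in year and applicable to Perth, on an immediate step, and on no differential protection from the control series. A smaller gap shrinks the bias in proportion. The documents do not show that a break is certainly built in. Because the sign and size of a named effect measure depend on an unstated counting rule, the rule should be settled before the outcome data are analysed.

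**What to change.** 1. State one dose-count rule for the primary outcome and apply it to both series and all 72 months, for example the first recorded HPV dose, with each person counted once in that month. Apply the same principle to the secondary outcome.
2. Align the Outcomes, Sample size and Data analysis wording with that rule.
3. Prespecify a sensitivity analysis that adds a level term at the start of 2023 to Models 1 and 2, allowed to differ between groups in Model 2. If 'fully vaccinated' is kept, make this the main model, including for the subgroup fits.

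The cost is wording plus one parameter per series; vaccination timing is already in the data request. The loss of precision is small. In Model 1 without harmonics, with AR(1) 0.3, the standard error of the level change goes from 0.622 to 0.630 SD. For the slope change under independence, the pre-period sum of squares falls from 9212 to 36 × (36² − 1)/12 + 12 × (12² − 1)/12 = 3885 + 143 = 4028, and the post-period sum is 24 × (24² − 1)/12 = 1150. The standard error therefore rises by a factor of √[(1/1150 + 1/4028)/(1/1150 + 1/9212)] = 1.07.

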•Level change at the end of the social media campaign (i.e. three months post the beginning of the social media campaign).•Change in slope.

In addition to the above model, for both outcomes, we will also fit the following single model (Model 2) that incorporates both the intervention and control series:

$$\text{Model}\;2:\log Y_{t}=\beta_{0}+\beta_{1}t+\beta_{2}I+\beta_{3}\left(t-T_{I}\right)I+\beta_{4}G+\beta_{5}\mathrm{tG}+\beta_{6}\mathrm{IG}+\beta_{7}\left(t-T_{I}\right)\mathrm{IG}+\text{seasonal}+\text{offset}+\epsilon_{t}$$
where

$Y_{t},T_{I},I,t,\text{seasonal},\text{offset and}\;\epsilon_{t}\;$
are as described above.

G
 represents the series with a value of 1 representing the intervention series, and a value of 0 representing the control series.

$\beta_{0}$
,

$\beta_{1}$
,

$\beta_{2}$
 and

$\beta_{3}$
 are as described above for the control series.

$\beta_{4},\beta_{5},\beta_{6}\;\text{and}\;\beta_{7}$
 represent the interactions between time and the intervention series. Specifically,

$\beta_{4}$
 represents the difference in the intercept at the beginning of the series between the intervention and control series,

$\beta_{5}$
 represents the difference in slope between the intervention and control series in the first segment,

$\beta_{6}$
 represents the difference in the level change between the intervention and control series, and

$\beta_{7}$
 represents the difference in the change in slope between the intervention and the control series.

We will compare the estimates of level change at the end of the social media campaign and change in slope between Model 1 and Model 2. This comparison will allow us to assess the possibility of whether a co-intervention/concurrent event may explain our findings.
^
35
^

We will plot interrupted time series graphs for all outcomes and series using the recommendations of Turner et al.
^
43
^ These plots will include: data points, trend lines, seasonality estimation and confidence intervals surrounding the trend line and counterfactual estimates. Segments will clearly delineated by breaks in the trend lines.

Subgroup analysis

We will fit Model 1 for the primary and secondary outcomes for the intervention series separately by:
•Sex (Females, Males)•Location in Perth (North West, North East, Central, South West and South East)

Influencer data

All qualitative information will then be synthesised descriptively, key messages will be identified, with thematic analysis completed using Nvivo software.

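### The stated 85% power fits a before/after mean shift without trend terms; under the planned segmented model a one-residual-SD level change at three months has about 40%

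*Protocol article*

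**What the plan says.** The only power statement is in the Protocol article, Sample size. It claims that the monthly series, 72 values in all, "will provide 85% power to detect a one-standard-deviation shift in the average proportions post-intervention". The significance level is 0.05, and the errors are taken as AR(1) with ρ = 0.3. The paragraph supports its choice of 0.3 with an empirical distribution of autocorrelations ("median 0.33; IQR 0.03, 0.58; 36 ITS studies in public health"). It does not say which regression model the calculation used, which standard deviation is meant, or whether the test is two-sided.

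The Data analysis section then plans something more elaborate: "A linear, segmented interrupted time series analysis will be used to evaluate the impact of the social media programme on HPV vaccination". Model 1 has an intercept, a pre-interruption slope (β1), a level change (β2), a change in slope (β3), two pairs of harmonics that are phase-shifted for one year, and lag-1 autocorrelated errors. The first effect measure is given as "Level change at the end of the social media campaign (i.e. three months post the beginning of the social media campaign"), and the second is the change in slope. Model 2 adds the control series and the corresponding differences β6 and β7. No power is given for any of these quantities.

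**The concern.** A shift in the post-intervention average is a difference of two means. The planned effect measure is a departure from an extrapolated trend, evaluated at one time point: β2 + 3β3. A step at the interruption is strongly collinear with a linear time term, so estimating the trend alongside the step inflates the standard error of the level change. A power figure for the first quantity does not carry over to the second.

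What is at stake is how the result is read. The 85% is the only indication of how informative the evaluation will be. If the power for the reported quantity is about half of that, an interval that includes no effect says much less than the Sample size paragraph leads a reader to expect.

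**Working it through.** **Inputs.** 72 monthly points, a one-SD effect, alpha 0.05 and AR(1) ρ = 0.3 (Sample size). The model terms, harmonics and effect measure come from Data analysis. The pre-period is given as "a pre-interruption period of 49 months, beginning on Jan 2020-Dec 2023", but those dates span 4 × 12 = 48 months; I used 48 pre and 24 post and tried the alternatives.

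**Assumptions.** Two-sided test; SD = residual monthly SD, set to 1; constant step on the linear predictor; ρ known; Gaussian approximation to the negative binomial log-link model.

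**Formulae.** SE(c′β) = √[c′(X′V⁻¹X)⁻¹c], with V the AR(1) correlation matrix. Power = Φ(1/SE − 1.96); the opposite tail is negligible at these values. Effect detectable with 85% power = (1.96 + 1.036) × SE.

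**Step 1: the stated figure.** X = intercept and post indicator. SE = 0.332, and power = Φ(3.012 − 1.96) = 85.4%. A hand check with the design effect (1 + 0.3)/(1 − 0.3) = 1.857 gives SE = √[1.857 × (1/48 + 1/24)] = 0.341 and power 83.5%. The stated 85% is reproduced.

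**Step 2: Model 1, same inputs.**

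| Quantity | SE | Power for 1 SD | SD detectable at 85% |
|---|---|---|---|
| β2, no harmonics | 0.622 | 36.2% | 1.86 |
| β2, plain harmonics | 0.646 | 34.0% | 1.94 |
| β2, phase-shifted harmonics | 0.632 | 35.3% | 1.89 |
| β2 + 3β3, no harmonics | 0.578 | 40.9% | 1.73 |
| β2 + 3β3, plain harmonics | 0.598 | 38.7% | 1.79 |
| β2 + 3β3, phase-shifted harmonics | 0.587 | 39.8% | 1.76 |

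At three months the SE is 0.578/0.332 = 1.74 times that of the mean-shift model.

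**Step 3: does another reading restore 85%?** With the residual SD, none that I tried does:
- Average post-period effect within Model 1: 39-40%.
- Common trend plus step, no slope change: 43%.
- 49/23 split without harmonics: 36% (β2) and 41% (three months). The 49/24 split, with or without harmonics: 34-41%.
- One-sided test: 46-53%.
- SD read as the innovation SD: 31-38%.
- ρ = 0: 50-59%. ρ = 0.58, the cited upper quartile: 27-33%.

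A simulation that also estimated ρ (1,500 runs) gave 84% for the mean shift, and 41% (interruption) and 47% (three months) for the segmented model. The segmented figures are inflated, because the test rejected a true null 8% of the time.

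**Step 4: if the SD is that of the raw series.** Let trend and season explain a share R² of the variance. The SE in raw-SD units is then 0.587 × √(1 − R²) at three months with phase-shifted harmonics:
- R² = 0.30: SE 0.491, power 53%.
- R² = 0.50: SE 0.415, power 67%.
- R² = 2/3: SE 0.339, power 84%.

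**Step 5: Model 2 contrast, series taken as independent.** With equal noise in both series the SE is multiplied by √2. At three months without harmonics, 0.578 × 1.414 = 0.818 gives 23%; for β6 alone, 0.622 × 1.414 = 0.880 gives 21%. The range is about 20-23%. With negligible control noise, the three-month contrast has at most the Model 1 figure, about 41%.

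**The case against.** The strongest objection is that the SD is undefined. School-based vaccination is seasonal and Model 1 removes seasonality, so one raw SD would be more than one residual SD. Step 4 shows how far this goes: power at three months nears 85% only if trend and season explain about two thirds of the variance. This stands as a limit on certainty, and it is why the 39-41% must be called conditional. It does not rescue the paragraph, which states no such assumption.

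Second, the 85% is not a miscalculation: it reproduces for the quantity that the paragraph names. This also stands. The defect is the mismatch with the planned effect measure. That a step-only model was used is an inference from the 85.4% match and from the wording about averages.

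Third, the equal-noise figure for Model 2 may be pessimistic. The control series is non-Aboriginal youth in the same city, presumably a larger group, although the paper gives no size. At a control-to-intervention noise ratio of 0.2 the contrast has roughly 33-40%, little below Model 1. The noise assumption therefore has to be stated with the figure.

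A reader might also turn the detectable effect into percentage points, using 89 youths a month and the coverage figures in the Introduction. The paper does not support that. The planned outcome is an overdispersed monthly count over the whole population aged 12 to 14, not a binomial proportion of those turning 15, and the coverage figures come from different populations (Perth Year 7, and national females turning 15).

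**Conclusion.** The concern holds in conditional form. With the stated inputs and the SD read as the residual monthly SD, the 85% belongs to a before/after mean shift without trend terms. The planned Model 1 has about 34-36% power for a one-SD level change at the interruption and 39-41% at three months; 85% power needs about 1.73-1.79 SD at three months and 1.86-1.94 SD at the interruption. The loss comes from estimating a trend together with a step, so it does not hinge on the month split or the sidedness.

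A reader might infer that the evaluation simply has 40% power, or that a null result will be reported as failure of the campaign. Neither follows. The power depends on an SD that the paper leaves undefined. The paper gives no decision rule for a null result, and it plans confidence intervals for the trend lines and counterfactuals. Power for the change in slope cannot be computed, because no slope effect is specified.

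**What to change.** In the Sample size paragraph:
1. Say which SD is meant: residual monthly SD, or SD of the raw series with the assumed share of variance explained by trend and season.
2. State power for Model 1 and the three-month level change: about 40% for one residual SD, or 85% for about 1.75 SD.
3. Say that the 85% for one SD applies only to a step model without trend terms, or remove it.
4. Give the matching figure for the Model 2 contrast (β6 + 3β7) with its control-noise assumption: about 20-23% if noise is equal in both series, at most about 41% if control noise is negligible.
5. Leave out any percentage-point conversion unless it is derived from the count model that will be fitted.

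The cost is wording and one recalculation. No data, design or analysis changes, and the campaign, already started, is unaffected. The price is a less favourable stated figure.
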